## Abstract

**Background:**

There is on one hand sufficient evidence showing strong association between resilience and self-rated successful aging. On the other hand, strength training could contribute the cultivation of resilience among older adults. Therefore, the current study aims to examine the effectiveness of resistance training on resilience among Chinese older adults in Hong Kong.

**Methods:**

This study will apply a three-group, double blinded (outcome assessors and data analysts), randomized controlled trial (RCT) to examine the effectiveness of the interventions on resilience, functional fitness, and health related quality of life immediately after a 16-week intervention, as well as the residual effects 12 weeks after completion of the interventions.

**Discussion:**

It is expected that resistance training is promising or even superior to aerobic training in the improvement of resilience. Given the limited evidence on the literature, it is urgently needed to explore the effects of resistance training on the improvement of resilience in older adults. Findings of the current study can contribute to the development of effective resistant training programs for the promotion of resilience among older adults.

**Trial registration:**

The trial is registered at the ClinicalTrials.gov PRS (Trial ID: NCT04690465; Date of First Posted: 30/12/2020).

## Background

With support from the health and medical research as well as technological advancement, the older population in the world has grown dramatically over the last several decades [1]. A similar situation was reported in Hong Kong. As of 2015, there were approximately 7.346 million people living in the city with a total of 1105 km^2^ of land. Among the 7.346 m population, 16% (1.17 m) was older adults (65 and over) [2], which has given Hong Kong many challenges in dealing with problems caused by ageing. Among the challenges, maintaining health related quality of life in the later years and reducing health related medical cost would be of great importance for both older individuals and the society. According to Rose and colleagues [3], aging is defined as a decline or loss (a “de-tuning”) of adaptation with increasing age, caused by a time-progressive decline of Hamilton’s forces of natural selection. Traditionally, older age has been viewed negatively as a time of frailty, disability, declining function, and greater physical and mental limitations. However, many older adults actually experience high wellbeing and quality of life and consider themselves to be aging successfully despite the onset of chronic conditions. It is believed that the combined psychological and physical characteristics of high resilience have the potential to facilitate the process of successful aging [4].

There is sufficient evidence showing strong association between resilience and self-rated successful aging [5, 6]. Resilience plays a critical role when older adults face the daily stress that comes from physical and mental loss with advancing age (e.g., changes in cognitive functioning, aging-related degradations in physical fitness), dysfunctional relationships with family members, increased isolation from society, and even the impact of extreme weather conditions [7]. There is considerable divergence in the literature in terms of construct and operational definitions of resilience. The focal point is whether resilience is a trait, an outcome or a process. During the past decades, some researchers held the view that resilience incarnates the personal qualities that empower individuals to thrive in the face of challenging circumstances. Resilience can be defined as the ability to bounce back or recover from stressful experiences, wherein ‘resilience’ derives from the Latin words salire (to leap or jump), and resilire (to spring back) [8]. Some scholars held the view that resilience as an outcome of successful adaptation despite challenging or threatening circumstances [9], or a class of phenomena characterized by good outcomes in spite of serious threats to adaptation or development [10].

In recent years, as research involved in the field increases, a growing number of researchers believe that resilience is a dynamic process encompassing positive adaptation within the context of significant adversity [11], which indicates that resilience is based on the balances between risk factors and protective factors. The American Psychological Association [12] defines resilience as the process of adapting well in the face of adversity, trauma, tragedy, threats or significant sources of stress — such as family and relationship problems, serious health problems or workplace and financial stressors. Current evidence supports viewing resilience as a universal dynamic process that helps individuals navigate their way in the context of exposure to stress using physical, psychological, social, and cultural resources that sustain their well-being [13] or an adaptive process that benefits maintaining, or swiftly regaining, homeostasis in conditions of stress [14].

Considering the significant meaning of resilience to older adults’ daily life, promotion of resilience among older adults is certainly worthy of lucubration. The promotion is even more urgent to Hong Kong given that one in three people will be 65 years old or above by 2036 [15]. Among the various influential factors on resilience, health-related lifestyles and higher functionality of individuals are identified as having strong associations with high resilience [16]. Moreover, regular exercise and/or physical activity (PA) has been found to be the key mediator within these associations [17]. Except for the well-established physiological benefits, psychological positive changes brought from resistance training should not be ignored. Recent evidence revealed the connections between resistance training and self-efficacy as well as social interaction among older adults [18]. During a 12-week program of moderate-to-high intensity resistance training, older adults reported a “good feeling” from doing resistance training. The “good feeling” might come from two facets. Firstly, resistance training is often stereotyped as being a young persons’ activity, many older adults are not educated in correct way to do resistance training. However, the older adults found out that they are not too old and stupid to do resistance exercise. They recognized their capabilities and showed improvement in self-efficacy. Secondly, the older adults might view the resistance training as part of the real life and gradually get a feeling of “taking control” of their life after repeatedly increased in workload during training. Furthermore, resistance training produced more training efficacy on increased resistance from the perspective of physiological stimulations.

Strength training was found to increase muscle strength by increasing muscle mass, and by improving the recruitment of motor units as well as increasing their firing rate in older adults. It was recommended that healthy old people should train 3 or 4 times weekly for the best results [19]. In a preliminary review, Windle [20] found a lack of publications that had adopted an intervention design in the studies of resilience in older adults. He further recommended that studies employing randomized controlled trial (RCT) design with specific intervention strategies as well as less robust evaluation using controlled trials should be conducted. MacLeod and colleagues [4] also found that the resilience interventions targeting older adults generally were not existing. They also found no tested interventions incorporating physical activity to build resilience among older adults, despite research suggesting that PA is an important factor of resilience.

Considering the above evidence, we may expect that resistance training is promising or even superior to aerobic training in the improvement of resilience. However, little evidence is found based on the literature and therefore it is a need to explore the effects of resistance training on the improvement of resilience in older adults. Based on the evidence of Windle [20] and MacLeod and colleagues [4], as well as the potential benefits of strength training contributes to the older people as indicated by Mayer and colleagues [19], the current study, adopting a RCT design, aims to examine the effectiveness of resistance training on resilience among Chinese older adults in Hong Kong.

## Methods

### Study design

This study will apply a three-group, double blinded (outcome assessors and data analysts), randomised controlled trial (RCT) to examine the effectiveness of the interventions on resilience, functional fitness, and health related quality of life immediately after a 16-week intervention, as well as the residual effects 12 weeks after completion of the interventions. The double blinding adopted in this study is to reduce the bias and to ensure that those who are collecting the outcome measures (such as research assistants collecting data via questionnaires and fitness assessors collecting data from the functional fitness test), and those who are inputting and analysing the data, have no knowledge regarding groups allocation status of the study participants [21].

In assigning the groups, the CONSORT procedure will be followed [22]. The three groups will be resistance training group, Tai Chi group, and control group. Tai Chi will be selected as an active concurrent control group for adding value in the comparison. The reason for choosing Tai Chi is because it has been proven to help the heart-failure patients improve their self-efficacy and self-esteem of resilience measured by the Resilience Scale [23]. Also, the aerobic type of Tai Chi will also demonstrate a bigger contrast to the anaerobic type of resistance training and therefore, the comparison on the training effects between resistance training and Tai Chi will add value to selection of exercise for future training and intervention of further study. Ethical approval from the Research Ethics Committee of the Hong Kong Baptist University has been obtained.

### Participants

The participants will be recruited from community senior service centers in Hong Kong by the approach of convenience sampling. Currently we are working with more than 30 community senior service centers locating in 18 districts in our ongoing research projects, in which a strong and supportive collaboration has been established for our recruitment of participants. The eligibility criteria for selection of subjects include: (1) 65 to 74 years old; (2) capable of walking without assistive device; (3) apparently healthy and live independently in communities; (4) no cardiovascular or related diseases that prevent from resistance training; (5) pass the PAR-Q screening or with physician’s advice on readiness of participation in resistance training; (6) no substantial experience in practicing resistance training or Tai Chi; and (7) low-to-moderate level of resilience. Participants with cognitive impairment, which will be determined by using the Chinese version of the Mini-Mental Status Examination (i.e., score < 24) [24] will be excluded. All participants will be recruited following the principle of voluntariness and their data will be kept confidential. Informed consent letters will be signed by the qualified participants prior to the commencement of intervention.

### Sample size estimation

Based on the previous intervention studies, the most frequently reported effect size was ranged from moderate (0.30) to high (0.70) [25–29], a moderate effect size at 0.30 will be adopted for the current study. To ensure an 80% probability for detecting a treatment difference at a two-sided 5% level of significance and taking into account a 20% of potential dropout rate [30], a sample size of 40 participants per group (totally 120 for 3 groups) will be required in the current study.

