### Grouping and randomization

Qualified participants who have signed a consent letter will be randomly assigned into three groups by a draw of lots, in a ratio of 1:1:1. The three groups will be 1) Intervention group: Resistance training (*n* = 40); 2) Active concurrent control group: Eight-form Yang-style Tai Chi program (n = 40); and 3) Non-treatment control group (n = 40). The CONSORT flow diagram is as follow:

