### Data analysis

Descriptive statistics will be used to describe baseline characteristics such as age, body weight, gender, resting heart rate, living status (alone or with family) of the participants in the study. The primary outcomes (resilience scores) will be analysed using an intention-to-treat (ITT) approach, and a sensitivity test will subsequently be conducted using the available data. Missing data will be replaced using the last observation carried forward method. For the secondary outcomes, per-protocol analysis will be conducted using the available data. The statistical significance level was set at *p* < .05. All data will be analyzed using SPSS Version 24.0 (IBM, Chicago, IL).

For the within group test, a one-way repeated measure analysis of variance (ANOVA) will be applied to each group to determine the changes of each outcome parameter among the three time points (i.e., pre-test, post-test, and follow-up test). When the sphericity assumption was violated, the Greenhouse–Geisser correction will be used when epsilon < 0.75, or the Huynh–Feldt correction will be used when epsilon > 0.75 [42]. Post hoc analysis with Bonferroni correction will be conducted to explore the differences between the pre-test and post-test, as well as post-test and follow-up test. The mean differences with 95% confidence intervals (CIs) will be reported. For the inter-group test, a one-way analysis of covariance (ANCOVA) with the baseline value as a covariate will be conducted at the post-test, and follow-up test to determine the group effect on each outcome parameter. Subsequently, the differences between the resistance training group and control groups as well as between the resistance training and Tai Chi groups will be analysed through planned contrasts. The effect size r was calculated manually according to r = sqrt [t2/(t2 + df)]. According to Cohen [43], r = .10, .30, and .50 represent a small, medium, and large effect size, respectively. The whole project is expected to complete within 18 months.

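### The 40 per group does not follow from the stated effect size of 0.30, whose metric is not named; the trial has 80% power only for fairly large pairwise differences unless baseline predicts outcome strongly

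*Protocol article*

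**What the plan says.** The Protocol article, Sample size estimation, reports that in earlier intervention studies "the most frequently reported effect size was ranged from moderate (0.30) to high (0.70"), and then that "a moderate effect size at 0.30 will be adopted for the current study". The remaining inputs are power ("To ensure an 80% probability for detecting a treatment difference"), significance ("at a two-sided 5% level of significance") and attrition ("taking into account a 20% of potential dropout rate"). The conclusion is that "a sample size of 40 participants per group (totally 120 for 3 groups) will be required in the current study". Grouping and randomization allocates the groups "in a ratio of 1:1:1".

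The section does not say whether 0.30 is a mean difference in SD units, a correlation-type r or Cohen's f. It also does not say which test or comparison was powered, or whether a correlation between repeated scores was assumed. The only effect-size metric defined in the article is in Data analysis, where r is computed from the t statistic and "r = .10, .30, and .50 represent a small, medium, and large effect size, respectively". The between-group analysis planned there is ANCOVA on the baseline value, separately at post-test and follow-up, followed by planned contrasts of resistance training with control and with Tai Chi.

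**The concern.** A sample size statement should let a reader get from its inputs to its number. Here the inputs are printed, the number is said to be required by them, and the straightforward calculations do not produce it. On one common reading, a standardised mean difference, the shortfall is a factor of 5.5 (220 / 40).

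The consequence lies in interpretation. The text promises 80% power for an effect it calls moderate. If the planned contrasts can in fact detect only fairly large differences, a non-significant result would be read as evidence against a moderate benefit when the trial could not have shown one. This matters most for resistance training against Tai Chi, where both arms are active and the article's Background hopes for superiority.

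**Working it through.** **Inputs** (Sample size estimation, Grouping and randomization): effect size 0.30, metric not stated; power 80%; two-sided 5%; dropout 20%; three equal groups of 40. Evaluable per group: 40 × 0.8 = 32.

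**Can the printed 40 be reproduced?** The evaluable number is n and the randomised number is n / 0.8.

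| Reading | Evaluable | Randomised | Power with 32 |
|---|---|---|---|
| Mean difference d = 0.30, two groups, exact t | 176 | 220 | 22% |
| r = 0.30, two groups, exact t | 41 | 52 | 70% |
| f = 0.30, omnibus, three groups | 37 | 47 | 74% |

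- *d:* the normal approximation is n = 2(1.96 + 0.84)² / 0.30² = 15.68 / 0.09 = 174.2, or 175. The exact t calculation gives 176, and 176 / 0.8 = 220.
- *r:* d = 2r / √(1 − r²) = 0.60 / √0.91 = 0.63. The exact t calculation gives 41, and 41 / 0.8 = 51.25, or 52.
- *f:* noncentral F with 2 numerator df and noncentrality N × 0.09. This gives 37 per group, and 37 / 0.8 = 46.25, or 47.

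**What does give 40, or close to it?**

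- d = 0.70, normal approximation: 15.68 / 0.49 = 32.0, and 32 / 0.8 = 40. The exact t calculation gives 34 (43 randomised), with 79% power at 32.
- f = 0.30 in an omnibus three-group ANCOVA, with an assumed baseline-outcome correlation of 0.4: 32, then 40.
- f = 0.30 in a repeated-measures between-group test with three time points and correlation 0.80: 32, then 40. At correlation 0.7 it is 38.
- f = 0.30 tested on one numerator df: 30, then 38, with 83% power at 32.
- r = 0.30 computed as in Data analysis, for a contrast within the three-group model (92 error df): t = √(0.09 × 92 / 0.91) = 3.02, with power 85% at 32.
- r = 0.30 in two groups gives 40 by the normal approximation only if dropout is left out, or if the test is one-sided. Both contradict the printed inputs.

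**What pairwise differences do these readings imply?**

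- For f = 0.30 in three equal groups, the gap between the extreme groups is 0.30 × 3/√2 = 0.64 SD if one group stands apart, and 0.30 × √6 = 0.73 SD if the means are evenly spread.
- For one-df f = 0.30, the noncentrality is √(96 × 0.09) = 2.94, so d = 2.94 × √(2/32) = 0.73.
- For contrast r = 0.30, d = 3.02 × √(2/32) = 0.75.

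**Effect of the planned baseline adjustment.** ANCOVA multiplies the residual SD by √(1 − ρ²). The article gives no baseline-outcome correlation, so ρ is an assumption.

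| ρ | Power for d = 0.30, 32 per group | Difference detectable with 80% power, 32 per group |
|---|---|---|
| 0 | 22% | 0.71 SD |
| 0.5 | 28% | 0.71 × √0.75 = 0.61 SD |
| 0.8 | 50% | 0.71 × 0.6 = 0.43 SD |

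The 0.80 quoted under Outcome measures is the resilience scale's test-retest reliability, not a baseline-to-16-week correlation. Entry is limited to low-to-moderate resilience, and a narrowed baseline range tends to lower the correlation, so 0.8 is a favourable value.

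**The case against.** The strongest reply is that the section never says 0.30 is a mean difference in SD units. The article's only defined metric is r, with .30 as medium, which matches the word moderate. Under r or f, power with 32 per group is 70% to 74% on the plain readings and 83% to 85% for a one-df contrast in the three-group model. With a suitable correlation, f = 0.30 gives exactly 40. Software settings of this kind are often omitted from a condensed article, and the cited studies that would settle the metric are not at hand. In addition, the primary analysis is intention-to-treat with last observation carried forward, so 40 rather than 32 per group would be analysed.

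Much of this stands. A reader might infer that 40 can only come from d = 0.70, and hence that the upper end of the cited range was used in place of 0.30. The documents do not support that: the f = 0.30 routes above also give 40, and d = 0.70 matches only under the normal approximation. A reader might also infer that the trial simply has 22% power. That holds only if 0.30 is a standardised mean difference, and only without baseline adjustment.

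The reply does not restore the printed derivation. The routes that reach 40 need a correlation or a one-df test that the section does not state. The repeated-measures between-group test is not among the planned analyses. Analysing all 40 raises power for d = 0.30 only to 26% unadjusted, and to about 33% and 60% at correlations of 0.5 and 0.8, before any dilution from carried-forward values. The favourable readings also work because they describe pairwise differences of about 0.64 to 0.75 SD.

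**Conclusion.** The point holds in a conditional form. The 40 per group cannot be derived from the inputs printed beside it. How far it falls short depends on the unstated metric: 220 per group would be randomised for a standardised mean difference of 0.30, 52 for a two-group r and 47 for an omnibus f, with power of 22%, 70% and 74% at 32 evaluable.

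The design's capability does not depend on what 0.30 was meant to be. With 32 evaluable per group, a planned contrast has 80% power for about 0.71 SD unadjusted and about 0.61 SD at an assumed correlation of 0.5. Only a correlation as high as 0.8 would bring this down to about 0.43 SD. These figures assume 20% dropout, equal groups, a common SD and a two-sided 5% test of each contrast. This goes beyond omitted detail, because a stated power and a stated requirement do not follow from their own inputs.

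**What to change.** Keep 120 participants and revise Sample size estimation as follows:

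1. Name the effect-size metric behind 0.30, the test and contrast that were powered, and any correlation assumed, and show the calculation. The authors should say which metric they used; the review should not choose one for them.
2. Replace the unsupported claim with what the planned contrasts can detect. Possible wording: *With 40 randomised and 32 evaluable per group, each planned contrast (resistance training versus control, and versus Tai Chi) has 80% power at a two-sided 5% level for a difference of about 0.71 SD without baseline adjustment, or about 0.61 SD if baseline and outcome correlate 0.5 (an assumption).*
3. Add that a non-significant contrast does not exclude a moderate difference, and that the confidence interval should be read for this purpose.

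The cost is wording only, with no extra participants and no change to the design. The drawback is that the stated detectable effect becomes less favourable than the present text suggests.

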### Grouping and randomization

Qualified participants who have signed a consent letter will be randomly assigned into three groups by a draw of lots, in a ratio of 1:1:1. The three groups will be 1) Intervention group: Resistance training (*n* = 40); 2) Active concurrent control group: Eight-form Yang-style Tai Chi program (n = 40); and 3) Non-treatment control group (n = 40). The CONSORT flow diagram is as follow:

### Training program design and implementation

With the support of the Physical Fitness Association of Hong Kong, China (PFA) and the Hong Kong Wushu Union (HKWU), it would expect that both resistance training and Tai Chi programs will be delivered safely and effectively by qualified coaches with professional monitoring.

